## **6.2 study intervention compliance**

Completion and use of the screening approach will be measured as key implementation outcomes via Aim 3. Specifically, we will measure:

1. Reach via record abstraction evaluating the proportion of eligible patients who completed SD screening and provider response on reasons for non-completion within 1 month of due.
2. Adoption via survey score of a 5-point scale on a survey at the conclusion of the study, asking (a) how often medical stakeholders reviewed SD screening results with relevant patients and (b) how often they discussed results with patients; a secondary measure of adoption will be results views by the provider (i.e. electronic health record (EHR) clicks)

# 7 STUDY INTERVENTION DISCONTINUATION AND PARTICIPANT DISCONTINUATION/WITHDRAWAL

## **7.1 discontinuation of study intervention (Study stopping rules)**

The Sponsor-Investigator has the right to terminate this study at any time. Reasons for terminating the study may include, but are not limited to, the following:

- The incidence or severity of adverse events in this or other studies indicates a potential health hazard to patients.
- Patient enrollment is unsatisfactory.

## **7.2 PARTICIPANT DISCONTINUATION/WITHDRAWAL FROM STUDY**

Participants are free to withdraw from participation in the study at any time upon request.

In addition, the investigator has the right to withdraw a patient from the study at any time. Reasons for withdrawal from the study may include, but are not limited to, the following:

- Patient withdrawal of consent/assent at any time
- Any medical condition that the Sponsor-Investigator determines may jeopardize the patient’s safety if he or she continues in the study.
- Sponsor-Investigator determines it is in the best interest of the patient.
- Patient non-compliance

Patients must discontinue study intervention if they experience any of the following:

- Discomfort
- Inability to complete surveys for any reason

Every effort should be made to obtain information on patients who withdraw from the study. The primary reason for withdrawal from the study should be documented on the appropriate eCRF.

## **7.3 lost to follow-up**

**Patient stakeholders** will be asked to complete surveys during their existing clinic visits immediately after consent/assent and enrollment. However, consent/assent, enrollment and surveys may be completed within 4 weeks of eligible visits (when sexual function screening are due).

# 8 STUDY PROCEDURES

## **8.1 study procedures/evaluations**

***ADAPTATION PHASE (Aim 1)***

**Study Design:** The prototype screening approach developed in prior studies will be implemented in the CHCO Neuro-Oncology clinic and undergo a multi-stage iterative test and revision process, guided by end-user feedback. We will test the screening approach through surveys on acceptability, appropriateness and feasibility with all participating patient and provider stakeholders. Surveys will consist of brief demographic data collection and adapted versions of three brief 4-item measures: Acceptability of Implementation Measure (AIM), Implementation Appropriateness Measure (IAM), and Feasibility of Intervention Measure (FIM) (details below and in Appendix 2), in conjunction with specific questions to elicit CFIR barriers/facilitators. We will also perform key informant interviews with a subset of medical stakeholders who score high and low on acceptability, appropriateness and feasibility surveys (interview guide available in Appendix 3). Field notes will also be collected by the research team.

Results will inform modifications to the screening approach by the research team, informed by stakeholder recommendations and use of the CFIR-ERIC (Expert Recommendations for Implementing Change) matching tool, which links CFIR barriers with implementation strategies to mitigate these barriers. Based on recommendations in the literature, we expect that this process will require 3-5 rounds of iterative modifications addressing stakeholder feedback. Each round will consist of 3-5 patient interviews, 3-6 medical stakeholder surveys, and 1-3 medical stakeholder interviews (total unique patients=9-25, medical stakeholder surveys=9-30 and interviews=3-15).^50^ Three stopping criteria will be used:

1. Saturation in key informant interviews regarding identified barriers/facilitators (i.e., no new unaddressed barriers/facilitators identified)
2. At least 80% of each group of stakeholders (patient, medical) surveyed will have scores of 4 or higher on the AIM, FIM, and IAM (indicating an average response of “agreeing” or “strongly agreeing” to items assessing the acceptability, feasibility, and appropriateness of the screening approach)
3. Stakeholders will identify no major problems with the screening approach (note that in the user-centered design field, “major problems” are defined as those which would severely limit the ability of end-users to implement the screen approach).

Once these stopping rules are met, the PI, mentors, and collaborators will produce a draft screening approach protocol and implementation package (e.g., use of a “clinical champion”, provider training, use of reminders in the electronic health record (EHR), flexibility for electronic or paper administration). If the stopping rules have not been met after 5 rounds, the research team will decide upon the screening approach protocol and implementation package based on feedback elicited through the 5th round.

Finally, a stakeholder focus group (n=6), recruited from prior medical stakeholders, will be convened to review the draft screening approach protocol (Appendix 4). Following this final feedback elicitation, the research team will produce the final screening approach protocol, implementation materials, and a Fidelity Checklist.

**Measures**: As outlined above, data collection will occur in multi-stage iterative testing via brief surveys and purposive focused interviews with stakeholders, focusing on RE-AIM implementation, acceptability, and feasibility, and potential CFIR-guided barriers and facilitators to these outcomes. Surveys will consist of three brief adapted 4-item measures: Acceptability of Implementation Measure (AIM), Implementation Appropriateness Measure (IAM), and Feasibility of Intervention Measure (FIM) (Appendix 2), in conjunction with specific questions to elicit CFIR barriers/facilitators. AIM/IAM/FIM are freely available and have demonstrated content and structural validity and test-retest reliability.^2^ CFIR-guided questions will elicit contextual factors in CFIR domains: 1) intervention characteristics (e.g., work flow compatibility), 2) outer setting (e.g., external policy), 3) inner setting (e.g., organizational culture), 4) individual characteristics (e.g., knowledge and beliefs about the intervention, provider role), and 5) process (e.g., key personnel). Qualitative interviews will inquire reasoning for respondents’ ratings as well as further explore CFIR factors (Appendix 3). Brief demographic data will also be collected for each participant.

**Data Collection**: Survey collection will occur in person at the end of patient encounters by the research team. Explanatory qualitative interviews will occur in person or by phone with medical stakeholders, by a trained qualitative research assistant (RA); these will be digitally recorded and professionally transcribed. Surveys and interview guides will be developed following the CFIR Interview Guide and will include items such as ease of use, compatibility with current clinic practices, and helpfulness/benefit. Iterations of the screening approach will be documented through detailed notes.

***HYBRID EFFECTIVENESS-IMPLEMENTATION PHASE (Aims 2-3)***

**Study Design:** We will use a pre-post hybrid effectiveness-implementation study design at 4 clinical sites.

Baseline, pre-implementation data collection will occur before the iterative intervention development in Aim 1 to avoid contamination. Following baseline data collection, the SD screening approach developed in Aim 1 will be implemented in three clinics and effectiveness data will be prospectively collected. All four sites will receive the intervention clinic-wide (for all patients meeting study criteria) and will contribute data in both the pre- and post-intervention phases. Thus, participants are part of a predefined group that will be “assigned” to receive the intervention by receiving care at the clinics where the intervention is being implemented. Prior to implementation of the screening approach, all relevant providers will be trained on the screening approach via a virtual training session, and any necessary practice-specific modifications will be made. Implementation strategies will be refined in Aim 1, but may include establishing clinical champions, EHR reminders, provider resources, and patient handouts.

In conjunction with Aim 2, we will use an explanatory sequential mixed methods design to measure implementation outcomes at each site during the post-intervention period. Quantitative data will be collected via surveys; patient stakeholder (n=43) outcomes will be assessed in real-time, within 1 month of screening completed/overdue during the implementation phase, whereas medical stakeholders (n=16-24) will be assessed post-implementation to avoid biasing providers while implementation of the screening approach continues. Quantitative analyses of implementation outcome data will be followed by a qualitative assessment to explain survey results, including exploration of multilevel barriers and facilitators to implementation via purposive interviewing with high- and low-rating stakeholders (n=10-15). At sites where only certain medical stakeholders are responsible for SD screening/follow-up, additional brief interviews assessing acceptability will be completed (n=5-10).

**Data Collection/Outcomes*:***

*Effectiveness*: Data will be collected prospectively on patients during the 3-month pre-intervention phase (n=43) and patients who receive SD screening within 1 month of it being due during the 3-month post-intervention phase (n=43) (total n=86). Additional data will be collected EHR, including documentation of and referrals for SD. Participants will complete a survey (Appendix 5) at the end of scheduled visits or via phone within 4 weeks of screening completion. The **primary outcome** is a patient-reported indicator that his/her provider has communicated with them about SD. We anticipate that most providers will only address SD with patients who report a concern on the SexFS Brief; this assumption is reflected in sample size calculations. However, because our preliminary work demonstrated that patients wanted SD conversations to accompany the SexFS Brief, our analysis will include all patients, regardless of SD screening results. **Secondary outcomes**, detailed in section 3, include patient satisfaction with SD communication^51^ and patient-report that an SD need was met. We will also assess the feasibility of collecting EHR data in all eligible patients via retrospective chart review (exploratory outcomes):

- Clinic/site
- Incidence of documented/detected SD
- Referral patterns to SD-related specialty care (fertility team, urology, gynecology/oncology, sexual health clinic, endocrinology, etc.) via EHR order or note documentation **(exploratory outcomes)**.

These secondary and exploratory outcomes will inform a future multicenter trial defining the clinical impact of our screening intervention. Brief demographic data will also be collected for each participant.

*RE-AIM Outcomes:* Data will be collected using a combination of quantitative patient (Appendix 5) and medical provider surveys (Appendix 6) purposive qualitative interviews with medical stakeholders, and research personnel observation (Appendix 7 and 8).^2,52^ For sites that choose to have a limited number of providers responsible for survey delivery and follow-up/management, only responsible providers will receive complete surveys. Surveys will be administered in person by the RA. Interviews will be completed in person or via telephone by the study’s qualitative RA using CFIR interview guides, similar to Aim 1.^48^

Details on assessment:

*Reach:* Reach will be assessed primarily through record abstraction evaluating the proportion of eligible patients who completed SD screening within 1 month of it being due. Secondarily, for patients who do not receive screening within 1 month of it being due, reach will be further explored via a single multiple choice question (Appendix 9) to the medical team inquiring into the reasoning for missed screening. *Representativeness* will be assessed by comparing sociodemographic characteristics between eligible patients who did versus did not receive screening (reported in aggregate/anonymously, corrected during the study eligibility screening process).

*Adoption:* **Medical stakeholder** adoption will be assessed via survey score of a 5-point scale on a survey at the conclusion of the study, asking (a) how often they reviewed SD screening results with relevant patients and (b) how often they discussed results with patients. If the EHR is used to deliver/report the survey (determined in Aim 1), we will explore objective measures, such as whether the results were viewed by the provider (i.e., clicks).

*Implementation:* Implementation will be assessed using four of Proctor’s implementation outcomes: *acceptability, appropriateness, feasibility and fidelity.^53^* These implementation outcomes will be measured from the perspectives of both patients and medical stakeholders, as well as via observation by the RA. **Medical stakeholder** outcomes will be measured at the conclusion of the study using the adapted AIM, IAM and FIM surveys in providers who are involved in SD screening/management; these surveys will also include basic demographic information (Appendix 6).^2^ At sites where there is a set group of responsible providers, acceptability will also be assessed among non-responsible providers in brief interviews (Appendix 8) **Patient stakeholders** who received the screening will complete patient**-reported** outcomes measures (5-point scale questions adapted from the AIM, IAM, and FIM (Appendix 5), as well as by the Fidelity Checklist developed in Aim 1).^52^ The Fidelity Checklist will also be completed through direct study personnel observation of the screening approach in 10% of patients across sites.^52^ Finally, study personnel will document adaptations to the screening approach as they occur throughout the study.

*Contextual Factors:* Guided by CFIR and using an explanatory mixed method design, we will complete 10-15 purposive interviews with **medical stakeholders** who rated the appropriateness, acceptability, or feasibility high or low to better understand contextual factors that serve as barriers or facilitators to use (Appendix 7). For example, to better understand feasibility, we will ask, “How did review of the screening tool fit into your workflow?” and follow up with direct questions about barriers, engagement, perceived successes/failures, and recommendations for improvement. Results will (a) help explain any observed variation in implementation outcomes across the three sites, and (b) inform selection or development of implementation strategies, informed by the CFIR-ERIC matching tool, to promote implementation across a variety of settings in our subsequent large-scale multisite trial.^54^

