**Exclusion Criteria**

An individual who meets any of the following criteria will be excluded from participation in this study:

1. Unable to read and speak English
2. Patients who did not receive cancer-directed therapy
3. Insufficient cognitive functioning to complete study measures, as determined by an oncology provider Participation in Aim 1 intervention development
4. Patients who did not undergo SD screening within 1 month of being due will be excluded from implementation outcomes (Aim 3)
5. Patient is at end of life or on hospice, as determined by an oncology provider

Consent and assent will consist of paper or REDCap consent/assent with waiver of parental consent and HIPAA waiver for participants <18 years old.

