*Post-Implementation:* The screening approach will be implemented across all eligible patients as part of clinical care. The research team will review eligibility of **patient stakeholders** through existing clinic schedules. Eligible patient stakeholders will be approached by research personnel at the end of each visit to present the study (prioritized), or by phone within 4 weeks of eligible visits (SD screening completed or overdue by 4 weeks or more), with a maximum of 3 attempts to reach potential participants. Study team members will be members of the Center for Cancer and Blood Disorder. Consenting/assenting participants completing the survey for data collection prior to leaving the clinic (preferred) or via REDCap emailed/MyChart/text link (n=43). We will again use a purposive consecutive sampling to achieve variation across the age categories (age 15-19 and 20-24), patient treatment status (on therapy or survivor), and gender, with final enrollment with a minimum 40% representation for each of these groups. Consent and assent will consist of a paper or REDCap consent/assent with waiver of parental consent and HIPAA waiver for participants <18 years old (when applicable – see section 10.1.1.2), presented in person or via email/MyChart/text after explanation of the study in person or over phone by research personnel. REDCap surveys will also be delivered in person or via email/MyChart/text after consent. Post-intervention, the survey will both effectiveness (all patients) and implementation (in those who received screening) (Aim 3, below); thus, participation will be compensated with a $20 gift card.

Research personnel will work with the study champions at each site to determine the best method to obtain **medical stakeholder** surveys (e.g., email, paper). Enrollment and consent of medical stakeholders will occur at the end of the post-implementation study phase, with all eligible medical stakeholders approached for participation in surveys (anticipating an 80% response rate, n=16-24). Medical stakeholders will receive $10 compensation for survey completion if the local site allows provider incentives. Medical stakeholder consent will be via REDCap postcard consent, with the opportunity to ask questions to research personnel.

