Sample Size: As a type 1 hybrid trial, this study is powered on Aim 2, but will explore preliminary implementation outcomes. Aim 3 **patient stakeholder** surveys will be administered in conjunction with Aim 2 post-implementation surveys to patients who received screening (maximum n=43). As this aim measures preliminary/exploratory implementation and is limited to those who received screening, we will not have a minimum sample size. Reasons for missed screening will be collected separately from providers. Aim 3 **medical stakeholder** surveys will be administered to consenting providers (anticipating an 80% response rate, approx. n=16-24), and Aim 3 semi-structured interviews with be completed with 10-15 providers directly involved in the screening intervention. At sites where only certain medical stakeholders are responsible for SD screening/follow-up, additional brief interviews assessing acceptability will be completed (n=5-10). Because the qualitative interviews will be focused on experiences with the screening approach and barriers/facilitators, we anticipate reaching thematic saturation with these sample sizes.^50^ User-centered design and qualitative research findings demonstrate that on average, 5 users/interviews will identify around 73-85% of all problems, and that groups of 10 find 95% of all problems (reaching near-saturation) when evaluating a design.^50,55^

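### Section 8.1 limits the post-phase primary sample to patients screened on time, while Sections 5.1 and 5.4 include unscreened patients and the pre-phase sample has no such condition

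*Protocol*

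**What the plan says.** Section 8.1, Data Collection/Outcomes, Effectiveness, describes the two samples for the primary outcome. For the first: "Data will be collected prospectively on patients during the 3-month pre-intervention phase (n=43". For the second: "patients who receive SD screening within 1 month of it being due during the 3-month post-intervention phase (n=43". The same paragraph times the phone survey from completion of screening, a date that an unscreened patient does not have. It also says that the analysis keeps all patients whatever their screening results; that concerns the result of screening, not its receipt.

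Other sections describe a wider post-phase sample:

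- Section 5.4, Post-Implementation, allows contact "or by phone within 4 weeks of eligible visits (SD screening completed or overdue by 4 weeks or more", and states that "the survey will both effectiveness (all patients) and implementation (in those who received screening".
- Section 5.1, exclusion criterion 4 for Aims 2-3: "Patients who did not undergo SD screening within 1 month of being due will be excluded from implementation outcomes (Aim 3". Aim 2 is not mentioned.
- Section 8.1, Study Design, has the 43 post-phase patients surveyed "within 1 month of screening completed/overdue during the implementation phase".
- Section 9.3 gives the Aim 3 patient surveys alongside the Aim 2 "post-implementation surveys to patients who received screening (maximum n=43", with no minimum. That fits a post-phase sample in which some patients were not screened.

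Section 9.2 puts no screened-only limit on the primary model. It assumes conversation rates of 5% before and 30% after, without saying whether the 30% applies to screened or to all eligible patients.

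**The concern.** The intervention is introduced clinic-wide, and Section 8.1 (Study Design) treats patients as assigned to it by attending an implementing clinic. The matching contrast is between all eligible patients before and all eligible patients after. If the post-phase group contains only patients who were screened on time, one side of the contrast is chosen by receipt of the intervention and the other is not.

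The barriers that Section 2.2 lists (discomfort, lack of privacy, family presence, limited time) could plausibly lead both to a missed screening and to no conversation. Removing such patients from one period only would turn the primary result into a per-protocol type of contrast, presented as preliminary clinic-wide effectiveness and carried into the planning of a multicentre trial.

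The wording matters at enrolment. An unscreened patient who is never surveyed has no primary outcome, so the analysis cannot restore that patient later. Two sites reading different sections could also build different cohorts.

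**Working it through.** **Inputs.** From Section 9.2: p1 = 0.05 pre, p2 = 0.30 post, two-sided alpha 0.05, power 80%, R² = 0.20 for the other predictors, N = 86 (43 + 43). Reach r, the share of eligible patients screened within a month of the due date, is itself an Aim 3 outcome and has no planning value in the protocol. The conversation rate u in unscreened post-phase patients is not given either. Both are assumptions below.

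**Step 1: reproduce the plan's figure.** Two-proportion formula with pooled null variance, p̄ = (0.05 + 0.30)/2 = 0.175:

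n per period = [1.96·√(2·0.175·0.825) + 0.8416·√(0.05·0.95 + 0.30·0.70)]² / 0.25² = (1.0532 + 0.4271)² / 0.0625 = 35.06.

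Total 70.1; divided by (1 − 0.20) this is 87.6, so 88 against the stated 86. With an effective 43 × 0.8 = 34.4 per period, power is 79.2%. The stated figure reproduces to within two patients.

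**Step 2: all-eligible post rate if 30% is the rate in screened patients.**

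p_all = 0.30·r + u·(1 − r), and difference = p_all − 0.05. Power uses the Step 1 method at 34.4 per period.

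| Reach | u = 5%: post rate | difference | power | u = 15%: post rate | difference | power |
|---|---|---|---|---|---|---|
| 100% | 30% | 25 points | 79% | 30% | 25 points | 79% |
| 90% | 27.5% | 22.5 | 73% | 28.5% | 23.5 | 75% |
| 80% | 25% | 20 | 65% | 27% | 22 | 71% |
| 60% | 20% | 15 | 47% | 24% | 19 | 61% |

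Example, 80% reach and u = 5%: 0.30 × 0.8 + 0.05 × 0.2 = 0.25, and 0.25 − 0.05 = 0.20.

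A screened-only sample would show 25 points in every row. The overstatement is (1 − r)(0.30 − u): 2.5, 5 and 10 points for u = 5%, and 1.5, 3 and 6 points for u = 15%, at 90%, 80% and 60% reach.

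**Step 3: the other reading, 30% as the all-eligible rate.** With u = 5%, the screened-only rate is (0.30 − 0.05·(1 − r))/r, which gives 32.8%, 36.3% and 46.7% at 90%, 80% and 60% reach. The all-eligible analysis then keeps the planned 79% power, and a screened-only sample would overstate the planned 25-point difference.

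**Step 4: limiting case.** At 100% reach the two cohorts coincide and nothing is overstated.

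**The case against.** The best reply is that most of the protocol describes the inclusive cohort. Sections 5.1, 5.4, 8.1 (Study Design) and 9.3 all point to unscreened patients being in the post-phase survey, and Section 9.2 adds no restriction. On that view one paragraph is out of step. This stands. A reader might infer from the Effectiveness paragraph that the primary comparison is screened-only by settled design and therefore inflated; the documents do not support that. They support a contradiction, and an overstatement only if that paragraph is followed and reach is below 100%.

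It is also fair to say that 5% may be too low for unscreened patients. All relevant providers are to be trained, and champions and patient handouts may be used, any of which could prompt conversations without a completed screen. The 15% columns allow for this: the gap shrinks but does not close.

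Two further inferences are tempting and are not made here. One is that recruitment itself favours screened patients because unscreened ones can be contacted only once four weeks overdue. In Section 5.4 that condition follows the phone route, while the prioritised approach at the end of the visit carries no such wording; four weeks also corresponds to the one-month allowance in Section 6.1.1. The other is that a screened-only cohort needs some minimum reach to fill on time. Section 9.2 gives only an approximate duration, and Section 4.3 ends Aims 2-3 on the number of patients, so low reach would lengthen recruitment.

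The protocol does collect reach, representativeness and reasons for missed screening. These would make selection visible but would not correct it.

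**Conclusion.** The concern holds as an internal contradiction over the post-phase population of the primary analysis. The Effectiveness paragraph of Section 8.1 conditions that population on timely screening, with no counterpart before implementation; Sections 5.1, 5.4 and 8.1 (Study Design) include patients whose screening was missed.

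If the Effectiveness paragraph governs and reach is below 100%, the estimate is selected on receipt of the intervention and probably too high for the clinic-wide effect. On the assumptions that 30% refers to screened patients and that unscreened patients report 5% to 15%, the overstatement is 1.5 to 2.5 points at 90% reach, 3 to 5 at 80% and 6 to 10 at 60%. Power for the all-eligible comparison is then 73% to 75%, 65% to 71%, and 47% to 61%. If the 30% already refers to all eligible patients, there is no power loss in the inclusive cohort. The protocol gives neither reach nor the unscreened rate, so no single figure can be fixed. The sample size calculation itself is sound on its stated inputs.

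**What to change.** - In Section 8.1, Effectiveness, define the post-phase primary cohort as all eligible consenting patients whose screening falls due in the post-implementation window, whether it was completed or is overdue. Reword the survey timing so that it also applies to patients without a completed screen. This brings the paragraph into line with Sections 5.1, 5.4 and 8.1 (Study Design).
- Label any analysis limited to screened patients as secondary and per-protocol.
- In Section 9.2, state whether the 30% refers to all eligible patients or only to those screened. If only to those screened, state an assumed reach and an assumed rate in unscreened patients, and restate the power.

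The cost is a change of wording made before post-phase enrolment. The drawback is that the stated power may become less favourable, as the table shows.
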